**Figure 2 F2:**
[figure not shown]
Study timeline according to Standard Protocol Items: Recommendations for Interventional Trials (SPIRIT) statement. eGFR, estimated glomerular filtration rate; SF-36, Short-Form 36.

### Sample size and recruitment

The feasibility of this study is assessed by analysing the prevalence of patients with CKD-PAD in the hospitals involved in this project. We identified a cohort of over 200 patients potentially meeting the inclusion criteria. In each centre, a network of physicians, including nephrologists, internists and vascular surgeons, will be established to identify potentially eligible patients and facilitate enrolment. Every centre will identify a responsible person for enrolment to assess patients’ eligibility and manage their inclusion in the randomisation list.

We calculated the sample size, hypothesising the superiority of the experimental treatment over the control group. A sample of 96 patients, 48 in each group, is needed to detect a 30 m improvement in 6 min walking distance in favour of the experimental group, assuming an SD of improvement of 30 m, with a type I error of 0.05 and a power of 90%. To account for possible dropouts, the sample size will be increased by 30%, resulting in a total of 124 patients to be enrolled.

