### Statistical methods

Standard methods for the analysis of RCTs will be employed. All analyses will be conducted using intention-to-treat, where any subject randomised to one arm remains in that arm regardless of whether they received the intervention.

Missing values, although we will make any effort possible to reduce their incidence, will be treated using the multiple imputation procedure. Moreover, a sensitivity analysis will be performed to assess the stability of the study’s conclusions, comparing the intention-to-treat analysis with an analysis that takes into account the level of participation in the intervention arm. A p value <0.05 will be considered statistically significant. Several statistical analysis software packages, including SPSS, MedCalc and Stata, will be used.

A Shapiro-Wilk test will verify the nature and distribution of the data. At baseline, the two groups will be compared in terms of demographics and primary and secondary outcome measures. Although our initial hypothesis suggested the superiority of the exercise group over the control group, to account for the possibility that participants in the control group might achieve better outcomes than those in the intervention arm, we will use two-tailed tests of significance for all analyses. For categorical variables, the χ^2^ test or Fisher’s test will be employed, as appropriate. Overtime between-group differences will be analysed using t-tests for symmetrically distributed data and analogous non-parametric tests, such as the Mann-Whitney test, for skewed data. A two-way repeated measures analysis of variance (factors: treatment, time) will be run to compare differences over time for secondary outcomes. Paired-sample t-tests or Wilcoxon tests will assess the within-group variations. Suppose a significantly different distribution between the two groups in the baseline outcome level is identified. In that case, a secondary analysis will be performed using multivariate modelling, such as analysis of covariance, to adjust for these factors. For the long-term outcomes, Kaplan-Meier curves with log-rank tests and Cox proportional hazard regression models will be performed.

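### The sample-size inputs as printed (30 m difference, SD 30 m, alpha 0.05, 90% power) require about 23 patients per arm, not the stated 48

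*Protocol article*

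**What the plan says.** The calculation is in the protocol article under Sample size and recruitment. The aim is framed as "hypothesising the superiority of the experimental treatment over the control group". The target reads "detect a 30 m improvement in 6 min walking distance in favour of the experimental group, assuming an SD of improvement of 30 m". Alpha is set at 0.05 and power at 90%. The result is given as: "A sample of 96 patients, 48 in each group, is needed". A 30% allowance for dropout is then added to the 96.

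The remaining inputs are elsewhere in the article. Under Outcomes, the primary endpoint is the change in 6 min walking distance from baseline to the end of the programme, so an SD of change is the right kind of SD. Under Allocation, the ratio is 1:1. Under Statistical methods, the sidedness is fixed ("we will use two-tailed tests of significance for all analyses") and so is the test: "Overtime between-group differences will be analysed using t-tests for symmetrically distributed data", with a rank test for skewed data.

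**The concern.** Every input to a standard two-group comparison of means is printed, and so is the result, so the calculation can be checked directly. A difference equal to one SD is a very large effect and needs few patients. Forty-eight per arm at 90% power belongs to an effect about two-thirds that size.

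This sentence is the article's only justification for the size of the primary comparison. As it stands, a reader cannot tell whether the trial was sized for 30 m or 20 m, or for an SD of 30 m or about 45 m. These readings differ in substance. If 30 m and 30 m are right, the trial plans about twice the evaluable patients its stated power needs. If the target was 20 m, the effect the trial was designed to detect is misreported. If the SD was about 45 m, the printed SD makes the design look more robust than it is. A null result, or a shortfall in recruitment, could not be set against a design target that contradicts itself.

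**Working it through.** **Inputs**

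- Difference in change between groups: 30 m (Sample size and recruitment)
- SD of change: 30 m (same paragraph)
- Type I error 0.05 and power 90% (same paragraph); two-sided (Statistical methods)
- Allocation 1:1 (Allocation); t-test between groups (Statistical methods)

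**Step 1: try to reproduce 48 per arm.** The normal-approximation formula is

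n per arm = 2 × (z for alpha + z for power)² × (SD / difference)²

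n = 2 × (1.960 + 1.282)² × (30/30)² = 21.01, rounded up to 22.

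The exact calculation with the noncentral t distribution gives power 0.8997 at 22 per arm and 0.912 at 23. The requirement is therefore 23 per arm, 46 in total. The stated figure is not reproduced: 96 / 46 = 2.09.

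**Step 2: power that 48 per arm gives with the printed inputs.** Exact t-test: 0.998.

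**Step 3: other settings, with the 30 m difference kept.**

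| Setting | n per arm (normal / exact t) |
|---|---|
| One-sided 0.05, 90% power | 18 / 18 |
| Two-sided 0.05, 90% power | 22 / 23 |
| Two-sided 0.05, 95% power | 26 / 27 |
| Two-sided 0.05, 99% power | 37 / 38 |
| Two-sided 0.01, 90% power | 30 / 32 |
| Two-sided 0.001, 90% power | 42 / 45 |
| 30 m taken as the SD of a single measurement, zero correlation (SD of change 30 × √2 = 42.4 m) | 43 / 44 |

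Allowing for a Mann-Whitney test, with efficiency 0.955 or 0.864 relative to the t-test, raises 23 to 25 or 27. None of these gives 48. Those that come closest contradict the printed alpha, the printed power or the wording that the SD is one of improvement.

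**Step 4: inputs that do give 48 at two-sided 0.05 and 90% power.** Solving the normal formula for the unknown:

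- SD, with a 30 m difference: 30 / 3.2415 × √(48/2) = 45.3 m
- Difference, with a 30 m SD: 30 × 3.2415 × √(2/48) = 19.9 m

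The exact t calculation puts the standardised effect at 0.669, that is, an SD of 44.8 m or a difference of 20.1 m. With the round pairs (30 m, SD 45 m) or (20 m, SD 30 m), the normal formula gives 21.01 × (1.5)² = 47.3, rounded up to 48. The exact t figure is 49.

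**Step 5: what depends on the SD.** Power for 30 m at 48 per arm, exact t-test. Only the first SD is from the article; the others are assumptions used to show the range.

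| SD of change | Power |
|---|---|
| 30 m | 99.8% |
| 45 m | 89.8% |
| 50 m | 82.9% |
| 60 m | 67.9% |

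**The case against.** The arithmetic is not in dispute. The strongest reply is that a mismatch does not prove a printed input wrong, because an article condenses a longer protocol and an input may have been left out. For illustration, testing superiority against a 10 m margin, with a true difference of 30 m and SD 30 m, leaves an effective difference of 20 m and gives 47.3, or 48 per arm, with every printed figure unchanged. Inflation for the six-monthly interim analyses could be suggested in the same way.

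This stands in part: the document cannot show whether the fault is a misprint or an omission. It does not rescue the sentence. The article mentions no margin, and the t-tests it describes compare the groups without one. No interim inflation is stated, and a factor of about 2.1 would be needed. Nor is this detail left to a fuller document, since the printed inputs and the printed result contradict each other.

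The other reply is that the error is conservative. On the printed inputs the trial has more power than claimed, and at an SD of 45 m it still has about 90%. A null result would also be read mainly from its confidence interval. That is fair, and the finding does not show an underpowered trial. The larger SDs in the last table have no support in the article. What remains is that the design target is unknown, and that is what the paragraph is there to state.

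**Conclusion.** The concern holds. With the inputs as printed, 23 patients per arm are needed (22 by the normal approximation), not 48. The stated number is about 2.1 times too large for 90% power, or equivalently the power at 48 per arm is 99.8%. This rests on the printed difference, SD, alpha and power, with 1:1 allocation and a two-sided t-test as the article specifies. Changing the sidedness, or allowing for a rank test, does not alter the conclusion.

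Whether 96 is too many patients depends on which figure is at fault. If the SD was really about 45 m, or the target about 20 m, then 48 per arm is right and the sentence misreports its basis.

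**What to change.** Go back to the calculation that was run and report its inputs, including any margin or inflation that was used. Two pairs would be consistent with 48 per arm at about 90% power: a 30 m difference with an SD of change of about 45 m, or a 20 m difference with an SD of 30 m. They show what to look for and should not be adopted merely because they fit. If 30 m and 30 m are the true inputs, keep 48 per arm and state the power as 99.8%. Adding that alpha is two-sided would tie the paragraph to the Statistical methods section.

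The cost is one corrected sentence, repeated wherever the same calculation appears. The 48 per arm need not change.

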### Allocation

After the recruitment procedure at baseline, the physician responsible for enrolment in the Coordinating Centre will create the allocation sequence on a password-protected computer. An external administrator not involved in the trial will then randomise patients to one of the two groups using a computerised randomisation stratification approach to prevent selection bias. The random assignment will be communicated to investigators on the day of enrolment by accessing it on identification in an online repository. Only one coordinator of each centre will be permitted to access the participants’ allocation. The randomisation scheme (1:1 ratio) will be established using permuted blocks of random sizes. The block sizes will not be disclosed to ensure concealment. Finally, the subjects will be assigned to one of two study groups: the exercise (Ex) group or the control (Co) group.

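### As written, the coordinating centre's enrolling physician creates the allocation sequence, so concealment is not ensured for patients enrolled there

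*Protocol article*

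**What the plan says.** The Allocation section of the protocol article describes these steps:

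- Creating the sequence: "the physician responsible for enrolment in the Coordinating Centre will create the allocation sequence on a password-protected computer".
- Assigning patients: "An external administrator not involved in the trial will then randomise patients to one of the two groups", by a computerised, stratified procedure.
- Release: "The random assignment will be communicated to investigators on the day of enrolment", through an online repository.
- Access: "Only one coordinator of each centre will be permitted to access the participants’ allocation".
- Scheme: "The randomisation scheme (1:1 ratio) will be established using permuted blocks of random sizes".
- Concealment claim: "The block sizes will not be disclosed to ensure concealment".

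The section on sample size and recruitment defines the enrolment role: "Every centre will identify a responsible person for enrolment to assess patients’ eligibility and manage their inclusion in the randomisation list". The section on study design and setting lists five sites, with Ferrara as coordinating centre, and has all of them enrol patients.

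**The concern.** Allocation concealment requires that whoever decides on a patient's entry cannot foresee the arm that the patient would get. Here the role that decides on entry at the coordinating centre is also named as the author of the sequence.

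Foreknowledge would leave room to steer, even without intent. Some entry criteria call for judgement: whether a patient can and will comply, whether comorbidity limits survival to under two years, and whether exercise is contraindicated. Timing is also flexible, because the Eligibility criteria section has candidates telephoned and then booked for an appointment. Someone who knows the next slot could affect who fills it without turning anyone away.

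The planned analysis would not repair this. Covariate adjustment is a secondary analysis, used only if baseline outcome levels differ significantly. It cannot remove selection on unmeasured traits such as motivation or likely adherence.

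**Working it through.** The point is procedural and the plan gives no figure to reproduce. The check sets the roles side by side and then tests each safeguard.

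**Roles**

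| Task | Who | Section |
|---|---|---|
| Assess eligibility, enter patients for randomisation | Person responsible for enrolment, one per centre | Sample size and recruitment |
| Create the sequence | Physician responsible for enrolment, coordinating centre | Allocation |
| Randomise patients | External administrator, afterwards | Allocation |
| See allocations | One coordinator per centre | Allocation |

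The first two rows carry the same role name, and the coordinating centre enrols. The natural reading is that one person does both tasks at that centre.

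**Safeguards, tested against the author of the sequence**

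1. The password keeps other people out of the file. It does not keep out the person who made it.
2. The administrator acts after the sequence exists. If the administrator applies the physician's sequence, the arms are already known to the physician. If the administrator generates the assignments independently, the physician's sequence has no stated purpose. The text does not say which applies.
3. Block sizes cannot be undisclosed to the person who creates the blocks.
4. The Allocation section opens by placing these steps after recruitment at baseline. This cannot mean after all recruitment has ended, because each assignment is released on the patient's day of enrolment. A permuted-block list therefore exists while recruitment continues.
5. The limit of one coordinator per centre governs who may look up allocations. It does not undo the author's knowledge.

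**How much foreknowledge this gives**

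A person who holds the sequence can foresee every assignment, against 50% correct guesses under full concealment with 1:1 allocation. Knowing only the block size and the earlier assignments in the same block already helps. The document withholds the block sizes, so sizes of 4 and 6 are assumed here.

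- Block of 4, best guess at each position: 1/2, then 2/3, then (2/3 × 1/2) + (1/3 × 1) = 2/3, then 1. The sum is 17/6 = 2.83 correct out of 4, or 71%.
- By simulation: 71% for blocks of 4, 68% for blocks of 6, 69% for a mix of 4 and 6. About 33%, 25% and 28% of assignments, respectively, are fully determined.

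These figures describe predictability. They do not measure bias in the 6 min walking distance.

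**Who is exposed**

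Each of the other four centres has its own enrolment person, and nothing says that they receive the sequence. The direct exposure is the coordinating centre's share of patients. The document does not give that share. If the five centres enrolled equally, which is an assumption, it would be 1/5 = 20%.

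**The case against.** The strongest reply is that the wording is loose and the process sound. The administrator is said to randomise patients by computer, which would be idle if the arms were already fixed. The recruitment section speaks of entering patients in a randomisation list, so the physician's sequence might be only the ordered list of entered patients. The sentences on blocks are passive and do not say who sets them. This reading is possible, but less natural than the plain text, which names the physician as creator of the allocation sequence. Even if it is right, the sentence names the wrong person and needs correcting.

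Other parts of the reply stand:

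- Many entry criteria are objective (kidney disease stage, Rutherford stage, cognitive score, haemoglobin, major amputation), which narrows the room for steering.
- That walking distance depends on effort is an issue of measurement and adds nothing to the concealment argument.
- Release after consent and baseline assessment is largely planned already. Both take place at one appointment, and allocation follows.

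A reader might infer that concealment fails across the whole trial, or that the bias can be put in metres. The document supports neither. Four of the five centres are not directly exposed. A figure in metres would need the share of patients exposed, the share of those steered, and the resulting difference in expected change between arms. None of the three is given.

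**Conclusion.** The point holds for the coordinating centre. Read as written, the plan lets one enrolling physician know the coming assignments and block sizes there, so its claim that undisclosed block sizes ensure concealment does not hold for that person. The other centres are affected only if the sequence is shared. The Allocation section also fails to say how the physician's sequence and the administrator's randomisation fit together.

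The size of any bias cannot be estimated from the document. The conclusion rests on two readings: that the enrolling physician is the person who assesses eligibility at that centre, as the shared role name suggests, and that the sequence means the order of treatment assignments. It does not show that anyone has used or would use such knowledge. The case for correction is that the text assigns the task to the wrong role, that selection at entry cannot be reliably undone in analysis, and that the remedy is nearly free.

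**What to change.** Rewrite the sentence so that the external administrator generates the sequence, including strata and random block sizes, and holds it in the online repository. State that nobody who assesses eligibility or enrols patients has access to the sequence or the block sizes. Keep the existing release of each assignment after consent and baseline assessment. The same rewrite removes the doubt about how the two steps relate.

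The cost is small: one task moves to a person already in the plan. The article does not give recruitment status. If a sequence is already in use, a wording change is not enough. The sponsor should then document who generated it and have the administrator generate the remaining sequence.

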### Blinding and data collection, management and analysis

Professionals in the management of the exercise programme will be responsible for outcome measurement, with one researcher assigned to each operational unit. An expert in data collection of body composition and bone mineral density will be responsible for collecting body composition parameters in every operating unit.

Two researchers blinded to the patients’ allocation will be responsible for entering the data into two electronic datasets, which will be compared with check for possible mistakes in data input. A password will protect every data set.

The researchers responsible for the statistical analyses will also be blinded to the patient group assignments. He will also be responsible for data management (quality control and data checking) and data analysis according to the different research hypotheses described.

Patient’s data will be treated following current regulations, including the 2016/679 European Union Act and D.Lgs. 30 June 2003, n. 196 s.m.i. Italian regulation, as well as any possible adjunctive measures deemed applicable by the Italian Data Protection Authority.

### Statistical methods

Standard methods for the analysis of RCTs will be employed. All analyses will be conducted using intention-to-treat, where any subject randomised to one arm remains in that arm regardless of whether they received the intervention.

Missing values, although we will make any effort possible to reduce their incidence, will be treated using the multiple imputation procedure. Moreover, a sensitivity analysis will be performed to assess the stability of the study’s conclusions, comparing the intention-to-treat analysis with an analysis that takes into account the level of participation in the intervention arm. A p value <0.05 will be considered statistically significant. Several statistical analysis software packages, including SPSS, MedCalc and Stata, will be used.

A Shapiro-Wilk test will verify the nature and distribution of the data. At baseline, the two groups will be compared in terms of demographics and primary and secondary outcome measures. Although our initial hypothesis suggested the superiority of the exercise group over the control group, to account for the possibility that participants in the control group might achieve better outcomes than those in the intervention arm, we will use two-tailed tests of significance for all analyses. For categorical variables, the χ^2^ test or Fisher’s test will be employed, as appropriate. Overtime between-group differences will be analysed using t-tests for symmetrically distributed data and analogous non-parametric tests, such as the Mann-Whitney test, for skewed data. A two-way repeated measures analysis of variance (factors: treatment, time) will be run to compare differences over time for secondary outcomes. Paired-sample t-tests or Wilcoxon tests will assess the within-group variations. Suppose a significantly different distribution between the two groups in the baseline outcome level is identified. In that case, a secondary analysis will be performed using multivariate modelling, such as analysis of covariance, to adjust for these factors. For the long-term outcomes, Kaplan-Meier curves with log-rank tests and Cox proportional hazard regression models will be performed.

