### Outcomes

Outcome measures will be collected at baseline (T0), after 6 months (T1), which corresponds to the end of the training programme for the experimental group, and at the 12-month (T2) follow-up by healthcare professionals blinded to patients’ allocation.

*The primary outcome* will be the measurement of the 6 min walking distance (6MWD) performed during the 6 min walking test.^41^ The variations in mobility assessed by 6MWD will be determined at the end of the programme in relation to the baseline. The patients will be instructed to walk back and forth along a 20 m corridor, aiming to cover as much distance as possible. Patients will also have to report the onset of any symptoms during the test, and the correspondent distance will be recorded as pain-free walking distance. When necessary, they will be allowed to stop as needed and restart whenever possible. Patients will also be monitored with a pulse oximeter to check their corresponding saturation. The rate of perceived exertion will be recorded on the 0–10 Borg scale at the end of the test.

*Secondary outcomes* will include the following:

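### The shape of the trial data decides whether the primary 6MWD comparison is a t-test or a rank test, so the quantity tested may not be the mean gain the trial was sized on

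*Protocol article*

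**What the plan says.** All references are to the protocol article.

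- Outcomes: the primary outcome "will be the measurement of the 6 min walking distance (6MWD) performed during the 6 min walking test", and the contrast is change over the programme: "The variations in mobility assessed by 6MWD will be determined at the end of the programme in relation to the baseline".
- Sample size and recruitment: 48 patients per group are "needed to detect a 30 m improvement in 6 min walking distance in favour of the experimental group". The spread of the change is also set at 30 m, and the error rates are 0.05 and 90% power. A difference in metres set against an SD is a difference in means.
- Statistical methods: "A Shapiro-Wilk test will verify the nature and distribution of the data". Later in the same paragraph, between-group differences over time are to be "analysed using t-tests for symmetrically distributed data and analogous non-parametric tests, such as the Mann-Whitney test, for skewed data".
- The same section confines repeated-measures ANOVA to secondary outcomes, makes ANCOVA a secondary analysis that is run only after a significant baseline difference, and uses paired tests within groups. All tests are two-sided, and missing values are multiply imputed.

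**The concern.** Once the other methods are set aside, the t-test/rank-test rule is what remains for the primary comparison. It leaves the choice of test to the observed distribution. It gives no cut-off for skew, does not say whether skew is judged per arm or pooled, leaves the alternative test open, and names no effect measure to report if the rank test is used.

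The two tests do not target the same quantity. The t-test addresses the difference in mean change in metres. Mann-Whitney addresses the probability that a patient in one arm does better than a patient in the other. They agree when the arms differ only by a shift, and can part when exercise alters the shape, for example if some patients respond strongly and others not at all. That is conceivable in a home programme, and the protocol itself plans an analysis by level of participation. The primary conclusion could then depend on which test the data selected, and a rank result would not say whether the 30 m target was met.

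**Working it through.** **The plan's own figure.** Per arm, n = 2 × (1.960 + 1.282)² × SD² / difference². With SD 30 m and difference 30 m, n = 2 × 10.51 × 1 = 21.0, or 22 after rounding up; the exact t-test also needs about 22 to 23. The stated 48 is not reproduced. It does follow from SD 45 m (2 × 10.51 × 2.25 = 47.3, rounded up to 48) or from a difference of 20 m with SD 30 m. That is a separate matter. Here it shows that the calculation is mean-based and that 48 per arm gives about 90% power for 30 m if the SD is 45 m.

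**What each test targets.** Let control change be normal with mean 0 and SD 30 m. Exercise-arm change is a two-part mixture, with SD 30 m within each part and the parts 100 m apart. The mixtures are assumptions, not taken from the protocol.

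- (a) 30% gain 100 m, 70% gain nothing. Mean = 0.30 × 100 = +30 m. Total SD = √(900 + 0.30 × 0.70 × 10,000) = √3,000 ≈ 55 m.
- (b) 15% lose 85 m, 85% gain 15 m. Mean = 12.75 − 12.75 = 0. Total SD = √(900 + 0.15 × 0.85 × 10,000) = √2,175 ≈ 47 m.
- (c) 10% lose 90 m, 90% gain 10 m. Mean = 9 − 9 = 0. Total SD = √(900 + 0.10 × 0.90 × 10,000) = √1,800 ≈ 42 m.

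The SD of a difference between two patients within components is 30 × √2 = 42.4 m. In (a), the probability that an exercise patient does better than a control is 0.70 × 0.50 + 0.30 × Φ(100/42.4) = 0.35 + 0.30 × 0.991 = 0.65. A pure 30 m shift with SD 30 m gives Φ(30/42.4) = 0.76 for the same mean gain. In (b) it is 0.85 × Φ(15/42.4) + 0.15 × Φ(−85/42.4) = 0.85 × 0.638 + 0.15 × 0.023 = 0.55, although the mean difference is zero.

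**Rejection rates.** Simulation with 48 per arm, two-sided 0.05, and 6,000 to 10,000 runs per scenario. The rule was modelled as Mann-Whitney if Shapiro-Wilk gives p < 0.05 in either arm, and a t-test otherwise. That threshold is also an assumption.

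| Scenario | t-test | Rule |
|---|---|---|
| Normal, no effect | about 5% | about 5% |
| Skew in both arms (15% lose 85 m, 85% gain 15 m), no effect | about 5% | about 5% |
| Same skew in both arms, 30 m shift | 88% | 93% |
| Gamma skew (shape 4, SD 45 m) in both arms, 30 m shift | 89% | 93% |
| (a) exercise only, mean +30 m | 92% | 75% |
| (b) exercise only, mean 0 | 5% | 11 to 12% |
| (c) exercise only, mean 0 | 5% | 9% |
| 50% gain 60 m, mean +30 m | 98% | 97% |
| 60% gain 50 m, total SD held at 30 m, mean +30 m | 99.8% | 99.7% |

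In (a) the two tests disagree in about 20% of trials. With normal data the modelled rule still moves about 10% of trials to the rank test by chance, without inflating type I error.

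**The case against.** Several objections have force.

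- **The gate is inferred.** A reader might infer that the protocol makes Shapiro-Wilk the formal switch for the primary outcome. It does not say so: the link rests on the order of the text, and the sentence on t-tests does not name 6MWD. This stands, so Shapiro-Wilk should be described as the apparent trigger. The choice still depends on how the data look, whatever the trigger, and the section leaves no other between-group method for the primary outcome.
- **Type I error.** A reader might infer that the rule inflates it in general. It does not: when the arms share one distribution it stays near 5%. The 9 to 12% figures are rejections at equal means but unequal shapes, where the rank hypothesis is itself false.
- **Value of the switch.** A reader might infer that it gains nothing. If vascular or renal events cause large losses in both arms, the rule has more power than the t-test. Scenarios (b) and (c) place the losses in the exercise arm only, and the Harms section expects major events to be rare.
- **Size.** The mixtures carry exercise-arm SDs of 42 to 55 m, against the planned 30 m. Milder responder mixes cost almost nothing.
- **Blinding.** Blinded analysts cannot readily choose a test to favour an arm. That is true, but blinding does not settle which quantity is tested.
- **An analysis plan may settle it.** How rank results would be pooled over imputations can be left to it, and the point does not rest on that. The data-dependent rule is not an omission, however; the protocol states it.

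**Conclusion.** The concern holds as a matter of what is being tested. The protocol states a distribution-based choice of test for the primary comparison, while the sample size rests on a difference in mean improvement. The harm is conditional. It is small under a pure shift, and skew common to both arms favours the rule. It is material if exercise changes the shape strongly: power of 75% against 92% at a mean gain of 30 m, and rejection in 9 to 12% against 5% of trials at no mean difference. These figures rest on assumed mixtures, 48 patients per arm, and an assumed Shapiro-Wilk threshold of 0.05 in either arm. The documents do not show that such mixtures will occur. The change should be made because it is cheap and ties the primary conclusion to the effect the trial was sized on; the documents do not show that the result would otherwise be invalid.

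**What to change.** In Statistical methods, name one primary analysis that does not depend on the observed distribution: the difference between arms in mean 6-month 6MWD, in metres with a 95% CI, from an ANCOVA adjusted for baseline 6MWD with robust standard errors, and pooled over the imputed data sets. Remove the distribution-based switch for the primary outcome. Report the rank comparison as a labelled sensitivity analysis.

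No extra patients, visits or measurements are needed, since baseline 6MWD is already collected. It is somewhat more than a rewording: ANCOVA moves from a conditional secondary analysis to the primary one. The sponsor also gives up some power if both arms share a strongly skewed distribution, about 5 percentage points in the assumed case above (88% against 93%, before any gain from baseline adjustment).
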